#### TEN Service Engagement

Engagement with TEN will be examined through survey questions provided to participants at the 1-month time point, as well as through website and service analytics. The questions will examine self-reported usage of TEN (Table 5). Website user analytics are automatically collected through the SAS CI 360 platform whenever a user interacts with the TEN website. These user analytics include the IP address of the user as well as which pages or resources were accessed and when. User analytics will be linked to the participant using the IP address provided during consent. TEN Clinic clinicians will also provide data from person-to-person clinical services, including whether a participant accessed the TEN Clinic and the number of sessions.

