#### Sample Size

Sample size calculations were based on the primary analysis: a random intercepts mixed effects model estimating change in WSAS scores from baseline to 1 month in a single group of participants. Estimated scores at baseline were derived from 249 TEN mental health assessments performed between June 28 and August 28, 2021. These scores represent HCWs self-selecting to engage with the TEN service and, as such, are analogous to the observational study participants at baseline. The mean of scores in this group was 14.9 (SD 8.9). The cut-off score for a clinical case on the WSAS is 11; thus, to reduce from the mean untreated score of 14.9 to a subclinical score requires a 3.87-point reduction. With variance-covariance of random effects derived from the SD in WSAS scores from current TEN users of 8.9, and accounting for 20% attrition, a sample size of at least 105 is required to detect a true reduction of this size with 80% power and a significance level of α=.05.

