### Study 2: Observational Study

#### Data Analysis

Descriptive statistics will be used to report the overall acceptability of TEN. The results from the observational study will be analyzed using linear mixed models to examine changes in reported psychosocial benefits over time (ie, baseline, 1 month). Patterns of service engagement and baseline outcome severity will be classified using cluster analyses or latent class analyses. These patterns will be used to examine how service engagement influences outcomes, as well as stratify participants baseline outcomes for subset analysis. Kaplan-Meier curves with TEN engagement data will be used to examine persistence with TEN over the course of the 6-month follow-up (ie, when participants ceased accessing the service). Missing data will be addressed using maximum likelihood estimation. This will answer the research questions by examining the acceptability of TEN among HCWs, patterns of service usage over time, any benefits observed after engaging with the TEN service, and persistence with the service over time.

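### The only stated test of how engagement relates to outcomes runs through data-driven classes in about 84 to 105 people; a direct usage term on counts already recorded should be added

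*Protocol article*

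**What the plan says.** The Study 2 Data Analysis section (under Results) plans linear mixed models for change from baseline to 1 month. On engagement it says "Patterns of service engagement and baseline outcome severity will be classified using cluster analyses or latent class analyses", and continues: "These patterns will be used to examine how service engagement influences outcomes". The same classes also stratify participants for subset analysis. The number of classes is not given.

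The only other mention of usage in relation to outcomes is in Potential Limitations. There, subgroup analyses by usage are offered as a partial view of improvement in people who did not use TEN. That too is categorical.

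Usage is recorded per participant in graded form:
- Website use is logged by page and time (Study 2 Data Collection; TEN Service Engagement).
- The 1-month survey asks for a numerical count of accesses (Table 5).
- Clinicians report "whether a participant accessed the TEN Clinic and the number of sessions".

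On size, the Sample Size section states that, "accounting for 20% attrition, a sample size of at least 105 is required". That figure was set for overall WSAS change, not for the engagement question.

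**The concern.** Sorting people into a few usage classes and comparing the classes discards the differences in usage within each class. It also spends a degree of freedom on every class beyond the first. In a sample this small, both reduce power when outcomes improve steadily with use. Usage counts are typically skewed, so a clustering algorithm may also split off a few heavy users, and a class contrast could then rest on very few people.

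Nothing in the data forces this step, because the counts exist and a mixed model is already planned. Study 2 has no control arm, so the usage comparison is the only internal view the article offers of improvement with and without TEN. A weak test here could leave a real gradient unseen.

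**Working it through.** **1. Sample available.** The plan's inputs are SD 8.9, 80% power, α = .05 (two-sided assumed) and this target: "to reduce from the mean untreated score of 14.9 to a subclinical score requires a 3.87-point reduction". Treating the two time points as uncorrelated:

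n = 2 × (1.960 + 0.842)² × 8.9² / 3.87² = 2 × 7.849 × 79.21 / 14.98 ≈ 83.0, rounded up to 84.

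With 20% attrition, 84 / 0.80 = 105. The plan's figure is reproduced exactly. The range for the engagement analysis is therefore 84 to 105 at the planned minimum; the plan says at least 105, so it could be larger.

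**2. Assumptions.** The documents give no usage distribution, usage-outcome correlation or number of classes. The simulations assumed correlations of 0.2 and 0.3 and 2 to 6 classes. K-means stood in for cluster analysis; latent class analysis was not simulated. Relative loss is 1 − (class power / direct-term power) within the same setting.

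**3. One usage measure, linear relation.** Usage was normal, a skewed count or a logged count. There were 600 replicates per setting, so the Monte Carlo standard error is at most √(0.25/600) ≈ 0.02.

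| N | Correlation | Power, direct term | Power, 2–5 classes |
|---|---|---|---|
| 84 | 0.3 | 0.81–0.82 | 0.55–0.66 |
| 84 | 0.2 | 0.42–0.49 | 0.25–0.35 |
| 105 | 0.3 | 0.87–0.88 | 0.63–0.74 |
| 105 | 0.2 | 0.53–0.55 | 0.31–0.41 |

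At correlation 0.3 the loss runs from 1 − 0.735/0.875 = 16% (N = 105, logged count, 3 classes) to 1 − 0.547/0.818 = 33% (N = 84, raw count, 5 classes). At 0.2 it runs from 1 − 0.408/0.537 = 24% to 1 − 0.247/0.443 = 44%.

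**4. Several usage measures clustered, with or without severity, 2 to 6 classes.** This is closer to the plan's wording. At correlation 0.3, power of 0.82–0.90 falls to 0.41–0.60 (loss about 32–50%). At 0.2, power of 0.43–0.58 falls to 0.17–0.32 (loss about 45–64%).

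**5. Noisier counts (n = 84, correlation 0.3).** With noisy visits, pages and Clinic sessions, log(1 + visits) had 46–52% power. Classes had 27–30% on raw counts (loss 36–46%) and 37–39% on logged counts (loss 18–29%). In a further run with 2 to 4 classes, log(1 + visits) plus Clinic use yes/no had 0.28–0.45 against 0.19–0.34 for classes.

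**6. Class sizes.** Three equal classes would hold 84/3 = 28 to 105/3 = 35 people. Across the runs in steps 3 and 4, the median smallest class was 19–48 people with 2 classes, 9–25 with 3, 7–18 with 4 and 5–13 with 5. It was 3–6 with 6 classes on several measures. In the noisy counts of step 5 it was 13, 6 and 2 on raw counts for 2, 3 and 4 classes, and 26, 11 and 9 on logged counts.

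**7. Non-linear relations (correlation ratio 0.3, three classes).**

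| True relation | N | Linear term | 3 classes |
|---|---|---|---|
| Benefit only in top third | 84 | 0.59 | 0.73 |
| Benefit only in top third | 105 | 0.69 | 0.84 |
| Middle third differs | 84 | 0.04 | 0.73 |
| Middle third differs | 105 | 0.04 | 0.83 |
| Peak in middle, part effect at top | 84 | 0.10 | 0.71 |
| Peak in middle, part effect at top | 105 | 0.12 | 0.82 |

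Here the class boundaries were placed exactly where the true effect changes, which is the best case for classes.

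**The case against.** **The choice is defensible.** TEN has several channels, and someone who visits once and then attends the Clinic is not simply a low-dose user. Patterns suit that structure, and step 7 shows that classes can win clearly. This stands as a reason to keep the classes. It is not a reason to omit a usage term: adding Clinic use yes/no covers the example, and the two-term model was level or ahead when the effect came only through the Clinic.

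**The counts are unreliable.** Potential Limitations concedes that linking by unique website link is prone to error. That may make the simulated gain too large. But the classes are built from the same counts. With website counts thinned at random, the usage term had 35–38% power against 24–31% for classes in most settings; two classes on logged counts were level or slightly ahead (41% against 38%).

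**A fuller plan may add detail.** Class number, handling of skewness and a supplementary dose term are often left to an analysis plan, and their absence from an article is no fault. The point here is the route that the article does state.

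**Stronger readings.** A reader might infer that the classes will each hold a handful of people, that about half the power is lost, or that a real gradient would usually be missed. The documents support none of these as general statements, because each needs a class number, usage distribution or effect size that they do not give. With one usage measure and correlation 0.3, classes still had 55–74% power. Nor does the text say that assigned class membership will be treated as known; latent class methods can carry that uncertainty.

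**Conclusion.** The point holds in limited form. The article commits to data-driven classes as its only stated route from engagement to outcomes, in about 84 to 105 people, while graded usage is recorded and left unused for this question. If the relation is roughly monotone and the correlation is 0.2 to 0.3, the class comparison gives up about one sixth (16%) to three fifths (64% at the extreme) of the power of a direct usage term. The lower end applies to a single measure, the upper end to several measures with a weak effect. Very small classes are a risk with skewed raw counts or many classes, not a certainty. Under a sharply non-monotone relation the order reverses.

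This is a secondary analysis and does not affect the primary WSAS comparison. A usage slope would be more precise but no more causal than a class contrast, since participants choose how much they use TEN.

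**What to change.** Keep the cluster or latent class analysis for usage patterns. Add one sentence to the Study 2 Data Analysis section along these lines: the linear mixed model for change from baseline to 1 month will also include a pre-specified measure of usage during the first month (for example log(1 + number of visits), and Clinic use yes/no) and its interaction with time; the slope will be reported with its confidence interval and read as an association, because usage is self-selected.

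The cost is one extra model on data already being collected. A linear term can miss a non-monotone pattern, which the retained classes would still show.

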### Potential Limitations

Although the implementation strategy has not yet been designed, the wide availability of TEN makes it difficult to examine site- or specialization-specific implementation strategies or service upgrades. Although the goal of TEN is to provide a blended care service for all Australian HCWs, this lack of specificity may hamper implementation within specific HCW specializations. The future of blended health is platforms that can be easily customized to different contexts, allowing for tailored implementation strategies and service upgrades. Similarly, the broad aims of the implementation of TEN may not be easily generalizable to other, more specific, contexts.

This implementation study and observational study will also be carried out during the ongoing COVID-19 pandemic. TEN itself was designed to support the mental health of HCWs during the pandemic. As such, changes in the COVID-19 context in Australia, such as outbreaks, restrictions, and the vaccination rollout, are likely to affect both uptake of the service and mental health outcomes. Such wider events will be considered when interpreting the results of both the implementation strategy and the observational study.

The observational study is also limited by a lack of an appropriate control arm and use of randomization. Common mental health outcomes, such as distress, anxiety, and depression, have the potential to improve over time without intervention. Although subgroup analyses examining usage of the service may shed some light on improvement without the use of the TEN service, the fact remains that a randomized controlled trial design with a suitable control would provide more robust data on efficacy.

Due to common concerns around mandatory reporting among HCWs [34], the TEN website was designed to be accessed anonymously (ie, without registration). Although this is a strength of the service itself, it poses problems for measuring participant engagement with the TEN website during a prospective study. The method used in the observational study—providing users with a unique website link—is error prone. Although participants are asked to bookmark the link and will be provided with the link via email, it remains that participants may simply access the TEN website without using their unique link. During data analysis, participant website analytics will be compared against self-reported usage to understand the extent of such errors.

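### Change read within baseline-severity classes carries regression to the mean, and unadjusted engagement classes cannot show that use influences outcomes

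*Protocol article*

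**What the plan says.** The Study 2 Data Analysis section names linear mixed models for change over time, with baseline and 1 month as the time points. It continues: "Patterns of service engagement and baseline outcome severity will be classified using cluster analyses or latent class analyses". On the use of the classes it says: "These patterns will be used to examine how service engagement influences outcomes, as well as stratify participants baseline outcomes for subset analysis".

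The Sample Size section confirms a single group and gives the WSAS figures: mean 14.9, SD 8.9, and "The cut-off score for a clinical case on the WSAS is 11". The target follows from these: "to reduce from the mean untreated score of 14.9 to a subclinical score requires a 3.87-point reduction".

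Potential Limitations admits that there is no control arm or randomization and that common mental health outcomes can improve without intervention. It adds that "subgroup analyses examining usage of the service may shed some light on improvement without the use of the TEN service". It does not mention regression to the mean in classes chosen on the baseline score.

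**The concern.** There are two separate biases.

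**Severity classes.** The baseline score that places a participant in a class is also the starting value of that participant's change. A class chosen for high baseline scores contains more people measured on a bad day, so its mean falls at the next measurement. A class chosen for low scores rises for the same reason. There is no control arm from which to estimate and subtract this. A mixed model with a class-by-time term estimates the same class-specific mean change, so it does not remove the effect.

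**Engagement classes.** Participants choose how much to use TEN. If those with worse baseline scores use it more, high users will show more fall than low users with no effect of use.

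At stake is the secondary reading of who benefits and whether use matters. The likely error is to conclude that TEN helps the severely affected, or does little for (or even harms) the mildly affected, when both patterns arise from selection on baseline.

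**Working it through.** **Inputs from the Sample Size section:** WSAS mean 14.9, SD 8.9, cut-off 11, target 3.87, 20% attrition, 80% power, α = .05.

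**Assumption:** the article gives no baseline to 1-month correlation ρ, so a range is shown. Scores are taken as bivariate normal with equal SDs and no true change.

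**Step 1: the plan's own figure.** n = 2 × [8.9 × (1.9600 + 0.8416) / 3.87]² = 83.02, rounded up to 84 completers. Then 84 / (1 − 0.20) = 105, which reproduces the stated figure. The match uses a variance of change of 2 × 8.9², the value for ρ = 0, so the sample size gives no guide to a realistic ρ.

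**Step 2: expected change in a class with no effect.** Expected change towards the overall mean = (1 − ρ) × |class mean − 14.9|. The distance of the class mean from 14.9 is 8.9 × φ(c)/(1 − Φ(c)) for a class above c, and 8.9 × φ(c)/Φ(c) for a class below it.

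- At or above 11: c = (11 − 14.9)/8.9 = −0.438, share 0.669, distance 4.82.
- Below 11: share 0.331, distance 9.76.
- Top third: distance 9.71.

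| Class | ρ = 0.5 | ρ = 0.7 | ρ = 0.8 | ρ = 0.9 |
|---|---|---|---|---|
| Top third, fall | 4.85 | 2.91 | 1.94 | 0.97 |
| At or above 11, fall | 2.41 | 1.45 | 0.96 | 0.48 |
| Below 11, rise | 4.88 | 2.93 | 1.95 | 0.98 |

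The top-third fall reaches 3.87 when 1 − ρ is at least 3.87/9.71 = 0.40, that is, when ρ is about 0.60 or lower. For the class at or above 11 it stays below 3.87 across this range.

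**Step 3: whole group.** At ρ = 0.5 the falls and rises cancel: 0.669 × 2.41 = 1.61 and 0.331 × 4.88 = 1.62, equal apart from rounding. The artefact redistributes change between classes and adds none overall.

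**Step 4: chance of a false finding.** Simulation with 84 completers, no true change, k-means classes on baseline WSAS and a paired t test in the most severe class gave these rates of significant improvement:

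| Classes | ρ = 0.5 | ρ = 0.7 | ρ = 0.8 | ρ = 0.9 |
|---|---|---|---|---|
| 2 | 0.76 | 0.52 | 0.37 | 0.22 |
| 3 | 0.87 | 0.63 | 0.44 | 0.24 |

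The whole-group test stayed at about 0.05.

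**Step 5: classes from several instruments.** The classes were then formed on the average of six instruments with independent errors, with true scores assumed to correlate 0.7 between instruments. The severe-third WSAS fall drops to about 1.2, 0.6 and 0.4 points at ρ = 0.5, 0.7 and 0.8. It shrinks but does not vanish.

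**Step 6: engagement.** Split users at the median of use and let use correlate b with the baseline score, with no effect of use. The spurious extra fall in high users is 2 × 0.798 × b × (1 − ρ) × 8.9. At b = 0.2, ρ = 0.8 this is 0.57 points; at b = 0.5, ρ = 0.5 it is 3.55. Simulation gave 0.59 and 3.52. If use follows the 1-month score instead, the sign reverses with about the same size. Both b and ρ are assumptions.

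**The case against.** Several counter-arguments stand in part.

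- The article does not say that pre/post change will be tested inside each severity class. Comparing engagement levels within severity strata also fits the wording, and would be a coarse form of baseline adjustment. Within-class change is still the natural reading, because change over time is the only outcome model named. The point is therefore conditional on that reading.
- A reader might infer that the plan relates 6 months of use to a 1-month outcome and so reverses time order. The documents do not support this. No engagement window is stated for the classes. The text ties the further 5 months of monitoring to persistence, and the mental health outcomes are collected again at 6 months. Reversed order arises only if use after month 1 is related to the month-1 outcome.
- A reader might infer that usage subgroups replace the control group. The sentence in Potential Limitations is hedged and ends by saying that a randomized trial with a suitable control would be more robust. It also concerns usage subgroups, so the severity-class figures do not describe it.
- The sizes depend on an unstated correlation and on how classes are built. Several instruments, which the wording allows, shrink the artefact considerably.

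What remains is that the general disclaimer about natural improvement does not cover this mechanism, which moves severe and mild classes in opposite directions.

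**Conclusion.** The point holds in a limited form. If change is read within baseline-severity classes, regression to the mean produces an apparent fall in the severe class and a rise in the mild class with no effect of TEN. On WSAS alone, the artefact could approach or exceed the 3.87-point target in a top-third class, but only if ρ is about 0.60 or lower. It is about 1 point at ρ = 0.9. To say that the severe class would show the planned effect goes further than the documents allow. An unadjusted comparison of change across engagement classes likewise does not show that use *influences* outcomes.

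These results rest on the article's mean and SD, a normal approximation and an assumed correlation. They concern secondary analyses only. The whole-group WSAS analysis and the sample size of 105 are not affected.

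**What to change.** 1. Estimate the engagement association in the whole sample, with the follow-up score as outcome and engagement and the baseline score as predictors.
2. Count only use that precedes the outcome analysed: visits between baseline and the month-1 survey for the 1-month outcome.
3. Examine severity through an engagement by continuous-baseline interaction, and drop pre/post tests within severity classes.
4. Treat any class-specific change as descriptive, and show beside it the change expected from regression to the mean over a range of correlations.
5. Write *is associated with* in place of *influences*. Baseline adjustment removes selection on the measured score, but not selection on other characteristics.

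The cost is a little more analysis work and a change of wording, with no new data. Subgroup improvements may look smaller.

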**Figure 3 figure3:**
[figure not shown]
Flowchart depicting a progression through the observational study. DQ-5: Distress Questionnaire; EASI: Endorsed and Anticipated Stigma Inventory; GAD-7: Generalized Anxiety Disorder; OBI-16: Oldenburg Burnout Inventory; PCL-5: Posttraumatic Stress Disorder Checklist; PHQ-9: Patient Health Questionnaire; SAS CI 360: SAS Customer Intelligence 360; TEN: The Essential Network; WSAS: Work and Social Adjustment Scale.

After consenting, participants will provide information on demographics and mental health (Table 2), service acceptability (Table 3), and complete baseline mental health and stigma outcomes (Table 4). Mental health outcomes are identical to the TEN online assessment. To avoid the participants needing to repeat the online assessment on the TEN website after completing the baseline mental health outcomes, the survey baseline will provide the same assessment feedback. Participants will then be provided with a link to the TEN website and asked to engage with the service naturalistically for 6 months. The link provided to each participant is unique and associated with their consent record number. User engagement (eg, pages viewed) with the TEN website is recorded automatically through the SAS Customer Intelligence 360 (SAS CI 360) platform. SAS CI 360 is a commercial website analytics package that records website use. Using unique TEN website links sent to participants, their TEN website use will be extracted and linked to their other study data. Participants will be recommended to bookmark this link, and their unique link will be provided to them by email at baseline and after the 1-month follow-up.

**Table 2 table2:** Questions examining demographic and baseline mental health.

Baseline question	Time point	Classification	Type of question
Gender	Baseline	Demographics	Single selection
Age	Baseline	Demographics	Single selection
Where are you located?	Baseline	Demographics	Single selection
What best describes your profession?	Baseline	Demographics	Single selection
Have you previously used the TEN^a^ service?	Baseline	Mental health	Yes/no
COVID-19 has affected your mental health.	Baseline	Mental health	Likert scale
Have you ever seen a doctor, counsellor, or other health professional about your mental health?	Baseline	Mental health	Yes/no
If you were seeking help for a mental health problem, what type of service would you most likely choose?	Baseline	Mental health	Multiple selection

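### The primary 1-month WSAS change assumes that drop-out depends only on the baseline score; engagement records, which exist for survey non-responders too, should inform the missing-data step

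*Protocol article*

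**What the plan says.** The Sample Size section of Study 2 names the primary analysis as "a random intercepts mixed effects model estimating change in WSAS scores from baseline to 1 month in a single group of participants". It takes a baseline SD of 8.9 and a target reduction of 3.87 points, and reaches at least 105 participants after "accounting for 20% attrition".

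The Study 2 Data Analysis section plans linear mixed models over baseline and 1 month. Its missing-data method is one sentence: "Missing data will be addressed using maximum likelihood estimation". The same section plans to classify patterns of engagement and says that "These patterns will be used to examine how service engagement influences outcomes". It does not say whether those patterns enter the model that gives the overall change.

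Engagement is captured without a survey reply. Under TEN Service Engagement, "Website user analytics are automatically collected through the SAS CI 360 platform whenever a user interacts with the TEN website", and clinicians report "whether a participant accessed the TEN Clinic and the number of sessions". Prior use of TEN is asked at baseline (Table 2), and the mental health instruments, including the WSAS, are repeated at 6 months. The Potential Limitations section concedes that tracking by unique link is error-prone and plans to compare it with self-reported use, which is asked only in the 1-month survey (Table 5).

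**The concern.** Maximum likelihood on two scores, with time as the predictor, in effect fills in a non-responder's 1-month score from the baseline score and the relation seen among responders. That is sound only if, among people with the same baseline score, responders and non-responders would have changed alike. Engagement is an obvious variable that could break this. The protocol regards it as potentially related to outcome, and much of the 1-month survey asks about the experience of using TEN, so people who barely used it have less reason to answer. Neither link is stated in the document; both are plausible assumptions.

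Study 2 has no control arm in which drop-out might balance, so any such bias enters the headline change directly. The information that could reduce it is already being collected, including for people who skip the survey.

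**Working it through.** **The plan's own figure.** For 3.87 points, SD 8.9, two-sided α = 0.05 and 80% power: n = 2 × (1.96 + 0.8416)² × 8.9² / 3.87² = 83.02, rounded up to 84. Then 84 / 0.80 = 105, which matches. The sidedness is not stated; two-sided reproduces the figure. The point here concerns bias, so 105 is not in question.

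**Inputs.** From the Sample Size section: n = 105, mean 14.9, SD 8.9, attrition 20%, target 3.87. Not in the document, so assumed and varied: the share engaged, the change by engagement, the drop-out by engagement, and a within-person correlation of 0.6.

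**Formula.** Let D_R and D_N be the mean falls in responders and non-responders. If engagement is unrelated to the baseline score, the model projects D_R onto everyone, so

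overstatement = 0.20 × (D_R − D_N).

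A gap of 1, 2 or 3.87 points gives 0.20, 0.40 or 0.77 points, which is 5%, 10% or 20% of the target.

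**Worked case.** Half are engaged, with falls of 5.80 and 1.94 and drop-out of 5% and 35%. The true mean fall is 0.5 × 5.80 + 0.5 × 1.94 = 3.87.
- Responders: (0.475 × 5.80 + 0.325 × 1.94) / 0.80 = 4.23
- Non-responders: (0.025 × 5.80 + 0.175 × 1.94) / 0.20 = 2.42
- Overstatement: 0.20 × (4.23 − 2.42) = 0.36

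**Simulation, 4,000 studies per row.** Falls are positive for improvement. Bias is estimate minus truth, so positive means improvement is overstated.

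| Engaged | Fall, engaged / not | Drop-out, engaged / not | True fall | Bias, formula | Bias, simulated | Bias with engagement used |
|---|---|---|---|---|---|---|
| 50% | 3.87 / 3.87 | 5% / 35% | 3.87 | 0 | +0.01 | +0.01 |
| 50% | 5.80 / 1.94 | 20% / 20% | 3.87 | 0 | +0.02 | +0.02 |
| 60% | 3 / 1.5 | 10% / 35% | 2.40 | +0.11 | +0.10 | −0.02 |
| 50% | 5.80 / 1.94 | 10% / 30% | 3.87 | +0.24 | +0.24 | 0.00 |
| 60% | 4 / 1 | 5% / 42.5% | 2.80 | +0.34 | +0.36 | +0.02 |
| 50% | 5.80 / 1.94 | 5% / 35% | 3.87 | +0.36 | +0.38 | +0.02 |
| 70% | 3.87 / 0 | 5% / 55% | 2.71 | +0.51 | +0.50 | 0.00 |
| 60% | 5 / 0 | 5% / 42.5% | 3.00 | +0.56 | +0.53 | −0.03 |
| 50% | 7.74 / 0 | 2% / 38% | 3.87 | +0.87 | +0.88 | +0.01 |
| 50% | −2 / 2 | 5% / 35% | 0.00 | −0.38 | −0.36 | +0.01 |

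The 60% rows use completer regression on the baseline score, evaluated at the full-sample baseline mean. The other rows fit the random-intercept likelihood directly. Coverage of the 95% interval is 91.7% in the worked case and 83.7% in the extreme case (7.74 / 0).

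**Imperfect tracking.** In the worked case, if 30% of engaged users are recorded as unengaged, using engagement lowers the bias from 0.38 to 0.20, so about half remains.

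**Precision.** In the 60% rows, adding engagement raises the standard deviation of the estimate by less than 4%.

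**The case against.** The strongest reply is that this is a condensed article, that maximum likelihood is an accepted method, and that lists of auxiliary variables and sensitivity analyses usually sit in a fuller document. Silence on those details would indeed be no finding. But the article does fix both the primary model and the missing-data method, and followed as written they carry the assumption described above.

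A reader might infer that the plan ignores engagement. The document does not support that: it plans outcome analyses by engagement pattern, and a model containing those classes and fitted by likelihood would condition on engagement. What it does not say is that the overall change estimate uses them.

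A reader might also infer that the 1-month improvement is biased upwards. That is not established either. No passage says that drop-outs are less engaged or improve less. The section describing TEN has users moving to person-to-person care where necessary, so heavier users could be those doing worse, and the bias would then run the other way.

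Two further points stand. First, the bias is modest beside sampling error. With 84 completers and correlation 0.6, the SD of change is 8.9 × √0.8 = 7.96 and its standard error 7.96 / √84 = 0.87, so all but the extreme scenario fall below one standard error. Unlike sampling error, however, it does not shrink with more participants. Second, recorded use is noisy and cannot be checked against self-report in people who did not return the survey, so the records are less complete than automatic capture suggests. The limitations section openly concedes the missing control arm and the tracking error.

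**Conclusion.** The concern holds in conditional form. The primary analysis as described is unbiased only if missing the 1-month survey depends on nothing beyond the baseline score that also bears on the 1-month score. If low engagement goes with both non-response and less improvement, the WSAS improvement is overstated by roughly 0.1 to 0.9 points at 20% attrition, against a 3.87-point target; the top of that range needs an extreme split. If either link is absent the bias is zero. The range rests on assumed engagement shares, changes and response rates, on a correlation of 0.6, and on engagement being unrelated to the baseline score. It shows how sensitive the result is and does not forecast the trial's result.

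The change is worth making because the relevant data are already held, no control arm can absorb the bias, and the cost is small.

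**What to change.** Keep the mixed model for the overall change from baseline to 1 month. Handle missing 1-month scores by multiple imputation, or by likelihood with auxiliary variables, using a short prespecified set: recorded website use, number of Clinic sessions, prior TEN use and the 6-month WSAS where available. These should inform the missing-data step only. Entered as covariates in the outcome model with a time interaction, engagement would turn the estimate into a change at a given level of use, which is a different quantity.

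Add one sensitivity analysis in which non-responders are assumed not to change from baseline. At 20% attrition, a fall of 3.87 in responders becomes 0.80 × 3.87 = 3.10, which shows readers how much of the result depends on those who did not answer.

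The cost is extra analysis work and a precision loss of a few percent. No new data or larger sample is needed. The correction will be partial because of the link-tracking error, and the report should say so.
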